#### Statistical analysis

The health economic evaluation follows a three-step procedure previously recommended for health economic analyses in Germany.^
47
^ Cost analysis employs a *difference-in-differences* (DiD) approach to compare trends in individual healthcare cost estimates between the intervention group and the control group, incorporating both direct and indirect costs.

In the first step, utility analysis is conducted using the DiD method to compare changes across the five utility dimensions at the individual level. Utility differentials are calculated between the four survey periods and subsequently compared between the IG and CG using hypothesis testing. For instance, for a patient *i*, the first differences in some utility index between periods 0 and 1 are

$$\Delta u_{i,1}:=u_{i,1}-u_{i,0},$$

With *μ*_i,0_ being the observation for the respective utility index at *T*_0_ for patient *i*. We check the null hypothesis that the utility differentials are not associated with whether the patients belong to the IG or the CG, that is, for

$$\Delta u_{i,t}=\delta I+\beta \prime x_{i},$$

we check

$$H_{0}:\delta =0.$$

Here, *I* is a binary variable that takes the value 1 for patients of the IG and 0 for those in the CG. **
*x*
**_i_

$x_{i}$
 is a vector of sociodemographic predictors. Those are included to avoid a potential bias in the test results because of heterogeneities between the two study groups. If the null hypothesis of interest can be rejected, the intervention is associated with different utilities than the standard treatment. The Greeks are parameters estimated based on the data via ordinary least squares.

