If the intervention does not lead to a deterioration in health utility, cost analysis will estimate cost differentials between the intervention and control groups using an approach similar to that applied for the utility dimensions. If the initial steps of the analysis do not demonstrate clear dominance of one care alternative over the other (i.e., neither intervention nor control prevails), cost-effectiveness analysis will be conducted, computing an incremental cost-effectiveness ratio (ICER). Analysis is conducted from the perspective of the SHI community, with the time horizon covering at least the study observation period. To address statistical uncertainty, stochastic sensitivity analyses will be performed using Monte Carlo simulations. These simulations generate empirical distributions of the ICER by simulating utility and cost indices 10,000 times. This approach provides an ICER distribution that can be used to estimate the probability of the intervention meeting prespecified cost-effectiveness thresholds, similar to methods described in Gillespie et al.^
48
^

ICERs will be calculated for all five utility dimensions to provide a comprehensive basis for healthcare decision-making. However, given the recognized importance of the EQ-5D index in health economic evaluations, recommendations for implementing the intervention into standard care will be primarily based on its cost-effectiveness analysis. The Monte Carlo simulations generate empirical distributions for both the utility (denominator) and cost (numerator) components of the ICERs based on 10,000 simulations of the overall cost and utilities change associated with the intervention through the observed period *T*_0_–*T*_4_. The nuisance parameters used for this are estimated by the earlier-mentioned regression models. For instance, the ICER in the trajectory *s* is:

$${\mathrm{ICER}}_{s}=\frac{\Delta u_{0-4,s,\mathrm{IG}}-\Delta u_{0-4,s,\mathrm{CG}}}{\Delta c_{0-4,s,\mathrm{IG}}-\Delta c_{0-4,s,\mathrm{CG}}},$$

with

$\Delta \mu_{0–4,s,\mathrm{IG}}$
: average utility differential between *T_0_* and *T_4_* for intervention group in trajectory *s*,
$\Delta \mu_{0–4,s,\mathrm{CG}}$
: average utility differential between *T_0_* and *T_4_* for control group in trajectory *s*,
$Dc_{0–4,s,\mathrm{IG}}$
: average cost differential between *T_0_* and *T_4_* for intervention group in trajectory *s*,
$Dc_{0–4,s,\mathrm{CG}}$

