: average cost differential between *T_0_* and *T_4_* for control group in trajectory *s*.

This approach generates a non-parametric distribution for the ICER, which can be compared directly to predefined cost-effectiveness thresholds and provide a recommendation, if the implementation of the intervention is given some willingness to pay.

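### Comparing simulated ICERs directly with a threshold does not give the probability of cost-effectiveness, because draws with a utility loss are not treated separately

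*Protocol article*

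**What the plan says.** All of this stands in the protocol article under Health economic evaluation.

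- **Sequence (Statistical analysis).** Utility changes are "subsequently compared between the IG and CG using hypothesis testing", with a null hypothesis of no group effect. Then: "If the intervention does not lead to a deterioration in health utility, cost analysis will estimate cost differentials". The ICER follows if neither alternative has been shown to dominate: "If the initial steps of the analysis do not demonstrate clear dominance of one care alternative over the other".
- **Simulation.** The Monte Carlo runs "generate empirical distributions for both the utility (denominator) and cost (numerator) components of the ICERs based on 10,000 simulations". The resulting distribution "can be used to estimate the probability of the intervention meeting prespecified cost-effectiveness thresholds".
- **Decision.** "This approach generates a non-parametric distribution for the ICER, which can be compared directly to predefined cost-effectiveness thresholds", and this is to lead to a recommendation at a given willingness to pay. The EQ-5D index is the dimension that mainly drives it.
- **Criteria (Aims and objectives).** Three conditions could justify routine use. The only one that refers to a cost-effectiveness threshold requires quality of life to improve while costs rise.

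Neither section mentions quadrants, negative ratios or net benefit.

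**The concern.** A ratio of two differences that can each take either sign has no consistent order. A low cost per unit of utility is good news only when utility is gained. Once simulated utility differences fall on both sides of zero, one cut-off on the ratio mixes the best results with the worst. The share of ratios below the threshold is then not the probability that the intervention is cost-effective.

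The ICER step is reached when the earlier steps have not settled the matter, which is when draws are most likely to spread over several quadrants. The probability read from them supports advice on routine care, so an error here could make an intervention with no benefit, or with a small harm, look like good value.

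**Working it through.** The article gives no probability, standard error or threshold, so there is no stated figure to reproduce. Steps 1 and 2 are free of assumptions; the later steps are illustrations.

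**1. Signs.** Cost over utility, with net monetary benefit NMB = λ × Δu − Δc at λ = EUR 20,000 per unit of utility:

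| Δu | Δc (EUR) | Δc/Δu | Below λ? | NMB |
|---|---|---|---|---|
| +0.02 | −300 | −15,000 | yes | 400 + 300 = +700 |
| −0.02 | +300 | −15,000 | yes | −400 − 300 = −700 |
| +0.02 | +300 | +15,000 | yes | 400 − 300 = +100 |
| −0.02 | −300 | +15,000 | yes | −400 + 300 = −100 |
| −0.02 | −1,200 | +60,000 | no | −400 + 1,200 = +800 |

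The first two rows have the same ratio and opposite value.

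**2. General result.** If Δu > 0, then Δc/Δu < λ is equivalent to NMB > 0. If Δu < 0, multiplying by Δu reverses the inequality, so Δc/Δu < λ is equivalent to NMB < 0. The rule is right for every draw with a utility gain and wrong for every draw with a loss. The misclassified share is therefore P(Δu < 0).

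**3. Inputs for the illustration.**
- From the Sample size section: 264 analysable patients, so 132 per arm; average cluster size 6 and ICC 0.05, so the design effect is 1 + 5 × 0.05 = 1.25. That ICC was set for the primary endpoint; using it for EQ-5D is an assumption.
- Assumed: SD of EQ-5D change 0.20 (range 0.15 to 0.25), cost SE EUR 400, zero correlation, λ = EUR 20,000.
- Utility SE = 0.20 × √(2 × 1.25/132) = 0.0275 (range 0.0206 to 0.0344).

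**4. Probabilities.** The correct value is Φ[(λ × Δu − Δc)/√((20,000 × 0.0275)² + 400²)], where the denominator is √(550² + 400²) = 680. The ICER rule gives P(NMB > 0 and Δu > 0) + P(NMB < 0 and Δu < 0), obtained here by simulating normal draws.

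| True (Δu, Δc) | Correct | ICER rule | Share misclassified | Correct / rule over SE 0.0206 to 0.0344 |
|---|---|---|---|---|
| (0, 0) | 50% | 80% | 50% | 50% / 75% to 83% |
| (0, +200) | Φ(−0.29) = 38% | 78% | 50% | 36% to 40% / 74% to 82% |
| (−0.02, +400) | Φ(−1.18) = 12% | 84% | Φ(0.73) = 77% | 8% to 16% / 86% to 84% |
| (+0.03, +300) | Φ(0.44) = 67% | 78% | Φ(−1.09) = 14% | 70% to 65% / 75% to 81% |

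**5. Other inputs.** With utility SE 0.02 and no true difference, the rule gives 65%, 75% and 88% at λ = 10,000, 20,000 and 50,000, against a correct 50% each time. The error can also run downward: at (+0.02, −300) and λ = 10,000, the correct value is 87% and the rule gives 81%.

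**6. The earlier steps, if read as significance tests.** Two-sided α = 0.05 is assumed; none is given.
- With both estimates 1 SE in the unfavourable direction, neither is significant, yet 0.841 × 0.841 = 71% of draws are worse and costlier.
- Power to detect a true utility loss of 0.05 is Φ(0.05/0.0275 − 1.96) = Φ(−0.14) = 44%, or 68% at SD 0.15 and 31% at SD 0.25.

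**The case against.** **The article does not say that negative ratios count as passes.** That is correct. A reader might infer that the plan declares worse-and-costlier draws cost-effective, but the text only calls for a direct comparison. The Aims and objectives tie the threshold to improved quality of life, both components are simulated so quadrants could be separated, and a fuller plan may do so. What remains is that the comparison as stated carries no such condition.

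**The gates might remove the bad cases.** If the earlier steps are read on point estimates, an observed (−0.02, +EUR 400) would be a deterioration with the control dominant, and no ICER would follow. The 84% in that row therefore arises only on the significance reading. That reading is plausible, because hypothesis tests are named, but no alpha is given and nothing states that non-significance means no deterioration. A reader might also infer that the gate causes the miscounting. It does not; at most it fails to prevent it. The three-step sequence is cited as a recommended procedure, and this point does not dispute it as such.

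**The error can be small.** In the case the threshold criterion was meant for, it nearly vanishes if the utility estimate is precise. At SE 0.015, which implies an SD of about 0.11, (+0.03, +EUR 300) gives 73% against 74%.

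**The printed formula is the other way up.** It puts utility over cost, against the text. That is a separate contradiction. It does not rescue the rule: set against 1/λ, dominant draws are negative and would fail.

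**Conclusion.** The point holds for the rule as written. The share of simulated ICERs below a threshold is not the probability of cost-effectiveness whenever some draws show a utility loss, and the comparison leaves out the article's own condition on quality of life. This follows from sign arithmetic alone.

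The size is not known. In the illustration the rule overstates the probability by 30 percentage points with no true difference and by 11 in the favourable case. These figures rest on assumed standard errors, zero correlation and an assumed threshold, and they shift with the true result. The weakness of the step 1 gate is secondary and depends on reading it as a significance test.

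This should be fixed before analysis. It affects the health economic conclusion only, not the primary endpoint, trial conduct or safety.

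**What to change.** - From the same 10,000 paired draws, compute NMB = threshold × Δu − Δc. Report the share of draws above zero over a range of thresholds as an acceptability curve, with the joint scatter of cost and utility differences. Base the EQ-5D recommendation on that, in place of the direct comparison of ICERs.
- For the other four dimensions, code each so that higher is better before doing the same.
- Run this analysis whatever the p-values in steps 1 and 2. Report the EQ-5D difference with its confidence interval, so that non-significance is not taken as evidence of no deterioration.
- Print the ICER as cost over utility, so that formula and text agree.

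The cost is analysis wording and code. No new data or further simulation is needed.

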### Process evaluation

#### Aims and objectives

The overarching goal of the process evaluation is to gain a comprehensive understanding of why and how the intervention succeeded or failed. To achieve this, both quantitative and qualitative data will be systematically collected from participants and extracted from the main trial’s study documentation.

#### Frameworks

The process evaluation follows the framework for process evaluations of cluster-randomized trials developed by Grant et al.,^
49
^ which outlines key steps of intervention implementation: participant recruitment, intervention delivery, and participant response at both the cluster and individual patient levels. Barriers and facilitators to sustaining the intervention over time, as well as any unanticipated effects, will be explored. To systematically identify and structure the barriers, facilitators, and mechanisms influencing intervention delivery, response, and maintenance, we will apply the updated Consolidated Framework for Implementation Research (CFIR),^
50
^ which encompasses five domains: innovation, inner setting, outer setting, characteristics of individuals, and the implementation process.

#### Research questions

Table 11 outlines the distinct research questions addressed by the process evaluation, investigated using both quantitative and qualitative methods.

**Table 11. table11-20420986251400042:** Overview of research questions to be examined by the process evaluation of the PARTNER cluster-randomized trial by intervention level and process step.

Process step	Research question(s)	Themes and parameters to be examined qualitatively or quantitatively (data collection from “main study” documents or bespoke “process evaluation”)
Cluster level		
Recruitment of clusters	How were clusters recruited?	Qualitative (inductive and deductive): Procedure and deviations, preselection, reasons for (non-) participation, support from study staff (process evaluation)
		Quantitative: Recruitment rate: proportion (%) of participating/invited doctors and pharmacists (main study)
	. . . how high is the willingness to participate?	Quantitative: Recruitment rate: proportion (%) of participating/invited GPs and pharmacists (main study)
	. . . what reasons play a role in participation?	Qualitative (inductive): Reasons for participation/non-participation (process evaluation)
	. . . who is taking part in the study?	Quantitative: Comparison of characteristics of participants/non-participants (main study)
Intervention delivery and response	. . . how were the intervention components implemented by the study staff?	Qualitative (inductive): Experience of the study staff from the training courses, level of knowledge, and previous experience of the doctors and pharmacists, necessary deviations from the specified procedure (process evaluation)
		Quantitative: type, number, and “severity” of deviations (main study)
	. . . what support was required to enable the service providers to implement the intervention components?	Qualitative: Type and effort of support provided by study staff (process evaluation)
		Quantitative: Number of contacts between study personnel and service providers (main study)
	. . . how are intervention components implemented?	Quantitative: Descriptive (number/type of empowerment brochures per patient; main study)
		Quantitative: Number/spectrum of identified ABPs in medication analyses (main study)
		Quantitative: Number of doctor/pharmacist contacts per patient (main study)
		Quantitative: Proportion (%) of patients with ⩾1 deprescribing attempt (main study)
		Quantitative: Number of (PSA-PIM-related) contacts with doctor/pharmacist (main study)
Maintenance at cluster level	. . . how do GPs/pharmacists assess the benefits and importance of intervention components? (How) do they influence behavior?	Qualitative (inductive): Justification of importance and usefulness/suggestions for improvement; Information on usefulness in semi-structured interviews (process evaluation)
	. . . what barriers do GPs/pharmacists identify for deprescribing, collaboration and intervention roll-out?	Information on implementation barriers in semi-structured interviews (process evaluation)
Patient level		
Recruitment of patients	. . . how high is the willingness to participate?	Recruitment rate: Proportion (%) of participating/invited GPs and pharmacists (main study)
	. . . who is taking part in the study?	Quantitative: Comparison of characteristics of participants/non-participants (main study)
Intervention delivery and response	. . . how are intervention components adopted?	Quantitative: Proportion (%) of patients who state that they were aware of the empowerment brochure on first contact with the pharmacist (main study)
Maintenance at patient level	. . . how do patients assess the benefits and importance of intervention components?	Qualitative (inductive): Justification of the importance and usefulness/Suggestions for improvement (process evaluation)
	. . . what barriers do patients identify to deprescribing and rolling out the intervention?	Qualitative (deductive and inductive): Type and significance of named implementation barriers/Proposed solutions (process evaluation)

GP, general practitioner; PSA-PIM, psychotropic, sedating, and anticholinergic potentially inappropriate medication.

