##### Patient screening and recruitment

GP practices will generate screening lists of patients meeting all the following inclusion criteria: age ⩾65 years, at least one GP visit in the quarter prior to inclusion, and use of ⩾5 active substances. The patient’s current medication will then be entered into a software tool, which applies an algorithm to identify the use of ⩾1 PSA-PIM. The software only notifies the GP practice whether the patient meets the inclusion criteria, without specifying the qualifying medication. To minimize selection bias, the remaining eligible patients are randomly assigned numbers and listed in ascending order. Starting with the first patient on the list, the GP verifies the exclusion criteria. Patients who remain eligible are then invited by the GP practice to participate in the study. If interested, informed consent will be obtained by the GP.

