**Figure 3. fig3-20420986251400042:**
[figure not shown]
Flow chart according to CONSORT. CONSORT, Consolidated Standards of Reporting Trials; GP, general practitioner.

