#### Dissemination

Within 1 year after completion of data collection, we will report results in ClinicalTrials.gov, including a flow chart of study recruitment and dropout, demographic and baseline characteristics of participants, primary and secondary outcomes, statistical test results, and adverse event information, if applicable. To make results available, we will provide the following: (1) Final report of the study results to the funder; (2) publication of study results in peer-reviewed journals; (3) presentations at national and international conferences; (4) plain language summary sent to patient participants.

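### Table 11 defines the patient-level recruitment rate by GPs and pharmacists, so it repeats the cluster-level measure and cannot show how willing patients were to take part

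*Protocol article*

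**What the plan says.** Table 11 (Process evaluation, Research questions) is split into a cluster-level and a patient-level part.

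- **Cluster level, recruitment of clusters.** The question on willingness to participate is answered by "Recruitment rate: proportion (%) of participating/invited GPs and pharmacists (main study", with the main study as data source.
- **Patient level, recruitment of patients.** The same question is answered by "Recruitment rate: Proportion (%) of participating/invited GPs and pharmacists (main study", again from the main study.
- **Patient level, next row.** The question of who takes part is answered by "Quantitative: Comparison of characteristics of participants/non-participants (main study".

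The section on patient screening and recruitment describes how patients enter. The practice lists patients by age, recent GP contact and number of drugs. A software tool flags those who use a target drug, and the flagged patients are put in random order. The GP then checks the exclusion criteria from the top of the list. The step that follows is: "Patients who remain eligible are then invited by the GP practice to participate in the study".

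On reporting, the Dissemination section promises results "including a flow chart of study recruitment and dropout". Figure 3 is captioned "Flow chart according to CONSORT", but its contents are not visible in the text at hand.

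**The concern.** A recruitment rate has to count the units that were invited. At patient level those are patients, yet the cell counts providers. Whatever value it takes, it carries no information on how many invited patients agreed.

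The patient rate is worth having. The Frameworks section adopts a scheme that looks at recruitment at both the cluster and the individual patient level, so the plan itself treats these as two questions. The random-order list is there to limit selection bias, but GP judgement still enters after it: two exclusion criteria in Table 2 rest expressly on the GP's assessment. Acceptance among invited patients, together with the number the GP excluded, is a natural check on how selected the final sample is. The patient-level text of the process evaluation ties generalizability to understanding which patients were included. It speaks of their characteristics rather than of acceptance, so the link to the recruitment rate is an inference, though a short one.

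**Working it through.** The article gives no figure to reproduce. It states targets of at least 44 clusters and 352 patients, but no number of invited providers or invited patients, so neither rate can be calculated from it. The check is a comparison of texts.

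**1. The two cells side by side.**

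| Row of Table 11 | Who is recruited | Numerator | Denominator |
|---|---|---|---|
| Cluster level, willingness to participate | GP practices and pharmacies | participating GPs and pharmacists | invited GPs and pharmacists |
| Patient level, willingness to participate | patients | participating GPs and pharmacists | invited GPs and pharmacists |

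The cells differ only in a capital letter and in the prefix marking the measure as quantitative, which the patient-level cell lacks. The first cluster-level row, on how clusters were recruited, also lists this rate, with doctors in place of GPs. Essentially the same rate therefore stands three times in the table, and the third time it is in the wrong place.

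**2. Is the right measure defined elsewhere?** No other part of the article defines a rate of participating over invited patients.

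**3. What the right measure would be.** Within one practice, take the recruitment steps in order and write

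- F = patients flagged as eligible by the tool,
- A = patients whose exclusion criteria the GP checked, working down the list,
- E = patients the GP excluded,
- I = A − E = patients invited,
- C = patients who consented.

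The measure that fits the row is C / I. None of these quantities involves the number of GPs or pharmacists invited, so the cell as printed cannot stand in for it.

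**4. The denominator for GP exclusions, if these are reported too.** Practices are told to recruit between 6 and 15 patients, so a practice may stop before the end of its list, and then A < F. Flagged patients who were not invited number

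F − I = F − (A − E) = E + (F − A).

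This mixes the GP's exclusions (E) with patients never reached (F − A). A ratio of invited to flagged patients would therefore overstate GP exclusion wherever the list was not exhausted, probably most in large practices. The sound ratio is E / A, with F − A given separately.

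**The case against.** The strongest objection is that this is a slip in one cell and that the counts may exist anyway. A reader might infer from Table 11 that the trial will never measure how many invited patients agreed. The documents do not support that. The next patient-level row plans to compare participants with non-participants, which requires non-participating patients to be identified. A flow chart of recruitment and dropout is promised with the results, the article commits to the CONSORT extension for cluster trials, and Figure 3 is such a flow chart with contents not shown. The article also condenses a full protocol that is not at hand. Whether invitations and consents are counted can be neither confirmed nor ruled out.

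This limits the consequence but does not remove the point. The cell is legible and complete, and it states a measure that does not answer its own question. That is a wrong statement, not a detail left to another document.

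Two further cautions stand. Nothing suggests that the authors chose to gauge patients' willingness through providers, so this should not be read as a design decision. And the screening section does not say that practices record refusals or exclusions by criterion, so the correction may need slightly more than existing paperwork.

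**Conclusion.** The patient-level recruitment rate in Table 11 is misdefined. As written it duplicates the cluster-level measure and cannot answer how willing patients were to participate. The finding rests on the wording of the two cells and on the stated recruitment procedure; it needs no numerical assumption.

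The size is small. A descriptive measure of the process evaluation is affected. The primary endpoint, the sample size and the primary analysis do not depend on it. If the flow chart reports patients invited and consenting, the information will be available whatever the cell says, and the error is one of labelling. If it does not, the patient acceptance rate could be missed, and it would be hard to reconstruct after recruitment has closed.

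**What to change.** In Table 11, patient level, recruitment of patients, redefine the rate as the percentage of invited patients who participate, with the main study as data source. Ideally summarise it per cluster. A split by arm adds little: clusters are allocated only once their patient recruitment is complete, so acceptance cannot respond to allocation.

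If GP exclusions are also reported, use as denominator the patients the GP assessed in list order, and count flagged patients who were never reached separately.

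The cost is one table cell. Practices that do not already keep a tally of invitations and refusals would need one, and reporting exclusions by criterion could need some extra documentation.
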